## Discussion

The main purpose of this study is to analyze the dose-response relationship between core-specific sensorimotor intervention programs of different training intensities and trunk function, represented by maximum strength capacity, sudden loading compensation and neuromuscular activity. Therefore, a feasible study protocol based on a single-blind randomized controlled design is used.

All training programs, control and all intervention groups, consist of core-specific sensorimotor exercises [10, 12, 23]. Moreover, additive sensorimotor perturbation will be applied to one (control group) and all exercises (all intervention groups) to enhance the efficacy of neuromuscular activity while exercising [24–26]. In a pilot study, Mueller et al. [25] showed that the use of additional perturbations during core-specific sensorimotor exercises was superior for enhancing trunk neuromuscular activity. Higher EMG amplitudes might indicate higher exercise intensity, but additional functional benefits and long-term effects still need to be investigated. Although convincing evidence exists for the relevance of sensorimotor exercises and their combination with additional perturbations to enhance core stability and trunk function, fundamental information on the dose-response relationship is rather sparse.

A main strength of the planned intervention programs is the overall short exercise duration as well as the low usage of resources in the home-based intervention [10]. This cost-effective intervention might be feasible for the transfer to the general population and/or elite athletes.

One main limitation in the trial presented here is the blinding of the participants. To keep the risk of bias to a minimum, all involved investigators are blinded to the group allocation.

In summary, the presented trial provides further insight into the dose-response relationship for core-specific sensorimotor exercises and the definition of a minimum dosage required to improve trunk function. In addition, the efficacy or non-efficacy of the sensorimotor exercises targeting neuromuscular factors like strength and neuromuscular activity will be evaluated in detail.

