In a pilot feasibility study (unpublished material, RCT (MiSpEx), German Clinical Trials Register No. DRKS00004977) including *n* = 750 participants, it could be shown that a core-specific sensorimotor exercise program (four exercises; nine sessions over 3 weeks; three sets of 10 repetitions per exercise) led to a significant increase in trunk function (strength gain) and pain reduction compared to a control group (no intervention). A compliance analysis revealed that more than one session per week (at least six sessions over 3 weeks) were necessary to achieve significant enhancement (function/pain reduction). In a recent Cochrane review on motor control exercises for non-specific low-back pain, Saragiotto et al. [10] summarized that the exercise programs’ duration ranged between 20 days and 12 weeks, with a number of sessions ranging from one to five per week. However, the exact determination of a valid dose-response relationship describing a reduced exercise amount and intensity necessary to improve trunk function remains unclear. Hence, the purpose of this study is to explore and compare the effect of three different 3-week (home-based) sensorimotor training programs in comparison to an evident control intervention, each varying the amount and intensity of training. Outcomes are maximum isokinetic trunk strength and trunk response (neuromuscular activity) to sudden, high-intensity trunk loading in healthy, normal, active adults.

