### Outcome measures

#### Trunk strength

The protocol consists of isokinetic strength testing of (right-sided) rotation as well as flexion/extension in a randomized order. Only right-sided rotation is tested due to the assumption of non-existing differences between sides in the cohort to be analyzed, as reported by Lindsay and Horton [15]. Trunk-strength rotation is measured in a seated position with a range of motion from 31.5° left-side to 31.5° right-side rotation (ROM 63°) using an angular dynamometer (CON-TREX WS, Physiomed Elektromedizin AG, Schnaittach, Germany) (Fig. 4a). Trunk flexion and extension is performed in a standing position using a second dynamometer (CON-TREX MJ/TP 1000, Physiomed Elektromedizin AG, Germany) (Fig. 4b). Participants are fixed to the dynamometer by adjustable adapters at the lower leg and knee, as well as by two non-stretching belts at the hip and upper body [16, 17]. Total range of motion is set at 55°, from 10° extension to 45° flexion.

Both conditions begin with an additional 60-s period of specific warm-up exercises and familiarization prior to testing. Maximum strength in rotation and in flexion/extension is tested in isometric (rotation: 0°; extension/flexion 17.5°), concentric (30°/s, con) and eccentric (30°/s, ecc) modes, performing five repetitions (5 s isometric) each. Furthermore, sudden dynamic loading is induced during eccentric mode (30°/s) by a novel, customized perturbation (acceleration from 30°/s to 330°/s within 120 ms for trunk rotation and from 30°/s to 150°/s within 250 ms for trunk extension). Verbal encouragement was given throughout the entire test to ensure participants’ maximum effort. The primary outcome of the study is trunk strength (peak torque) analyzed for all test modes including peak torque (Nm) in trunk rotation, trunk flexion and trunk extension, calculated as the mean of the three highest peak torques out of five repetitions [16, 17]. In previous studies, high relative (intraclass correlation coefficient (ICC)) and absolute (TRV and Bland and Altman bias and limits of agreement) reproducibility could be shown for isokinetic trunk peak torque and response to sudden, dynamic trunk-loading assessment (peak torque with perturbation: ICC 0.94, test-retest variability 8.53 ± 6.33%; bias ± 1.96 SD: 8.16 ± 64.8 Nm; *n* = 10) [18–22].

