### Statistical analysis

A power analysis to calculate sample size was not performed. The number of subjects to be included was based on previous published studies [13, 14]. *N* = 20 subjects per group will be included.

Data is collected and analyzed after the assessment is completed. After the plausibility check, the data is descriptively analyzed, including the means and standard deviations (SD) of torque (primary) and EMG (secondary) outcomes. In addition, a gain score analysis (change score analysis) using the mean difference between M1 and M2 for between-group differences of the outcomes will be performed (one-way analysis of variance (ANOVA)).

All statistical procedures are executed after the examination of underlying assumptions for parametric and non-parametric hypothesis testing. Hypotheses testing for all outcomes are performed using particular variance analytical testing (e.g., two-way ANOVA with dependent samples). The level of significance is set at *α* = 0.05 for all statistical analyses. Multiple testing will be controlled via Bonferroni adjustment.

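### The aim of defining a minimum dosage is not supported by the planned tests: neither a non-significant difference from an active control nor a pre/post gain without an untrained arm can show that a reduced programme is sufficient

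*Protocol article*

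**What the plan says.** The Background describes the gap as a valid dose-response relationship "describing a reduced exercise amount and intensity necessary to improve trunk function remains unclear". It gives the purpose as to "explore and compare the effect of three different 3-week (home-based) sensorimotor training programs in comparison to an evident control intervention". The closing paragraph of the Discussion goes a step further: the trial is to provide insight into the dose-response relationship and "the definition of a minimum dosage required to improve trunk function".

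Under Study design and flow, all four groups, control included, receive three weeks of training. There is no untrained arm.

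The Statistical analysis section states "A power analysis to calculate sample size was not performed" and "The number of subjects to be included was based on previous published studies"; "20 subjects per group will be included". The inference named there is a one-way ANOVA of gain scores between groups and, as an example, a two-way ANOVA with dependent samples. On error control it says "The level of significance is set at *α* = 0.05 for all statistical analyses", with Bonferroni adjustment over a family whose size is not given. The section states no effect size, no acceptable loss against control and no rule for calling a dose the minimum.

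**The concern.** To call a reduced programme enough, relative to a control programme already held to work, is to claim that it is not unacceptably worse. A test of difference can show that arms differ; it cannot affirm that claim. With small arms and a multiplicity adjustment, a real deficit will often go undetected.

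The conclusion at stake is the practical one. The Discussion counts short duration and low use of resources as a main strength and looks to transfer to the general population and elite athletes. If a non-significant result were read as adequacy, a weaker programme could be recommended without evidence that it suffices.

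**Working it through.** **What the plan gives.** There is no power figure to reproduce. The protocol fixes 20 per arm and four arms, so the pooled error has 4 × 19 = 76 df, and alpha is 0.05 (taken as two-sided).

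**What has to be assumed.**
- True deficit against control: 0.5, 0.8 or 1.0 SD of the gain score.
- Bonferroni family: 1 (unadjusted), 3 (each reduced arm against control) or 6 (all pairs).
- Scale in Nm: the Trunk strength section quotes "bias ± 1.96 SD: 8.16 ± 64.8 Nm" for peak torque with perturbation, n = 10. This gives SD of retest differences = 64.8/1.96 = 33.1 Nm. It applies to that test only, and the SD after training could be larger.

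**Precision of one arm against control.**
- SE = SD × √(2/20) = 0.316 SD, or 33.06 × 0.316 = 10.45 Nm.
- 95% half-width = t(0.975, 76) × SE = 1.992 × 0.316 = 0.63 SD, or 20.8 Nm.
- Dunnett for three comparisons: 2.394 × 0.316 = 0.76 SD, or 25.0 Nm.

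**Chance that a true deficit is non-significant** (noncentral t, 76 df, noncentrality = deficit/0.316):

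| True deficit | Noncentrality | Unadjusted | Bonferroni 3 | Bonferroni 6 |
|---|---|---|---|---|
| 0.5 SD | 1.58 | 0.655 | 0.800 | 0.863 |
| 0.8 SD | 2.53 | 0.295 | 0.465 | 0.566 |
| 1.0 SD | 3.16 | 0.123 | 0.239 | 0.326 |

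By normal approximation, the chance of a miss falls to 50% at 1.96 × 0.316 = 0.62 SD unadjusted, at 0.76 SD with Bonferroni 3 and at 0.83 SD with Bonferroni 6.

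**The pre/post route.** The time factor of the two-way ANOVA could show a gain within an arm. The retest bias quoted above, 8.16 Nm, is 8.16/33.06 = 0.25 SD. The protocol does not give its direction. If it is a practice effect, it would appear as improvement in any arm at any dose, and no untrained arm is available to subtract it.

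**What a margin would require.** Take true equality with control and one-sided 0.025. By normal approximation, a margin of 0.5 SD has 35% power with 20 per arm (21% with Bonferroni 3), and 80% power needs 63 per arm (84). The smallest margin with 80% power at 20 per arm is (1.96 + 0.84) × 0.316 = 0.89 SD, or 1.02 SD with Bonferroni 3.

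**The case against.** A reader might infer that the trial will declare a reduced programme sufficient whenever the ANOVA is non-significant, so that the plan is biased towards the smallest programme. The protocol does not support that. It contains no such rule, and non-significance is not the only route to a minimum dose. A dosage required to improve can mean improvement over baseline, and the pilot described in the Background used similar language about the sessions needed for significant enhancement. On that reading low power works the other way: an arm of 20 with a true gain of 0.5 SD reaches significance in about 56% of trials at 0.05 and 33% at 0.05/4. This objection stands against any fixed direction of bias. It does not rescue the aim, because the pre/post route lacks an untrained comparator.

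The stated purpose is to explore and compare, and the Discussion sentence can be read as offering only insight. The reduced arms also add perturbations to every exercise, so they could do better than control, and a two-sided comparison is reasonable. Both points stand. They bear on how firmly the aim is worded and on which test is run; they do not supply a basis for naming a sufficient dose.

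It would also be too strong to say that a clearly weaker programme would usually be missed. This holds at 0.5 SD. It fails at 0.8 SD unadjusted (30%) and at 1.0 SD in all three settings (12-33%). Finally, the 33.1 Nm comes from ten people in one perturbation test, whereas the primary outcome covers rotation, flexion and extension in several modes. A single margin or half-width in Nm for all of them has no support.

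Rules for interpreting intervals may stand in an analysis plan that is not shown. The point here is narrower: the aim, the tests and the sample size that the article does state do not fit together.

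**Conclusion.** The point holds as a mismatch between aim and inference. Neither a non-significant difference from an active control nor a within-arm gain can establish that a reduced programme is enough. At 20 per arm, the risk of missing a deficit against control is about 65% (unadjusted) to 86% (Bonferroni 6) at 0.5 SD, 30-57% at 0.8 SD and 12-33% at 1.0 SD. These figures rest on assumed effect and family sizes, normally distributed gain scores, a common variance and no dropout. The Nm figures apply to the perturbation test only. This is a cheap improvement to what the trial may conclude; the comparison of arms itself is not invalid.

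**What to change.** Before the data are seen by group:

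1. For each reduced programme against C, report the difference in peak-torque change with simultaneous (Dunnett) 95% confidence intervals.
2. State that neither a non-significant ANOVA nor a within-arm gain will be read as showing that a programme is sufficient.
3. Choose one of two routes. Either limit the minimum-dosage statement to exploratory estimation, or call a programme sufficient only if its lower limit lies above minus a margin that is justified and fixed separately for each primary test mode.
4. State the expected 95% half-width in SD units of change: about 0.63 SD, or 0.76 SD with Dunnett. Give 21-25 Nm for the perturbation test only.

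The first, second and fourth steps cost wording and one extra table. The margin route costs more: at this sample size most arms are likely to be reported as inconclusive unless the margin is near 0.9-1.0 SD, and a loss of that size may be hard to defend as acceptable. A tighter margin needs more participants, for example 63 to 84 per arm for 0.5 SD at 80% power. If that is out of reach, the exploratory wording is the simpler choice.

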## Methods/design

### Study design and flow

The study is designed as a single-blind, four-armed, randomized controlled trial with two identical measurement days (M1/M2), in which participants are allocated to either the experimental groups or the control group. All groups, interventions as well as control, receive 3 weeks of core-specific sensorimotor training organized in different home-based protocols. Potential participants are screened and examined by a sports medicine physician before baseline assessment and randomization to the groups to determine eligibility. Participants’ maximum trunk strength and trunk response to sudden, high-intensity trunk loading is assessed at baseline and after the 3-week intervention phase (Figs. 1 and 2; Additional file 1). All adverse events will be monitored and reported.

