#### Intervention groups and control group

Control and intervention group participants are instructed to perform six training sessions during the 3-week, home-based training phase. However, the number of exercises and sets per exercise vary between the control group and all intervention groups. Training frequency and number of exercises per group are detailed in Table 1.

**Table 1 Tab1:** Intervention and control groups: details of training frequency and number of exercises per group

Group	Intervention	Total amount of sessions	Total time per session	Number of exercises	Sets per exercise
Control group C	MiSpEx protocol	6	30 min	4 (rowing, side plank, bird dog, standing balance)	3
Intervention group I G I	Better than nothing	6	20 min	3 (rowing, side plank, bird dog)	2
Intervention group II G II	Half-way done	6	10 min	2 (side plank, bird dog)	2
Intervention group III G III	Only once	6	5 min	1 (side plank)	3

The control group performs a standard protocol consisting of four different sensorimotor core-specific exercises (Table 2). All four exercises will be performed with three sets of 10 repetitions each, with a minimum of 30 s rest in between sets (unpublished material, RCT (MiSpEx), German Clinical Trials Register No. DRKS00004977, [13, 14]). In between exercises, a 2-min break (self-controlled) is allowed. The exercises are commonly described as: (1) bird dog; (2) deadlift/rowing; (3) single-leg stance and (4) side planks. Two of the exercises, bird dog and side plank, are dedicated to directly training the core-stabilizing and/or core-surrounding muscles while the other two exercises, deadlift/rowing and single-leg standing balance, are considered to impact the core indirectly by means of the upper and/or lower extremities. To account for possible side effects, side plank and single-leg stance are always performed at ten repetitions each side.

**Table 2 Tab2:** Exercise details: for each exercise, level (1–3), surface (stable/unstable) and description including perturbation are provided

	Exercise 1: bird dog		Exercise 2: deadlift/rowing		Exercise 3: single-leg standing balance		Exercise 4: side planks	
					
Exercise Level	Task	Perturbation	Task	Perturbation	Task	Perturbation	Task	Perturbation

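### All four arms train, so the trial can compare programmes but cannot by itself show that any of them works or which minimum dose improves trunk function

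*Protocol article*

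**What the plan says.** The design has no untrained arm. Under Study design and flow: "All groups, interventions as well as control, receive 3 weeks of core-specific sensorimotor training organized in different home-based protocols". Under Intervention groups and control group: "The control group performs a standard protocol consisting of four different sensorimotor core-specific exercises". Table 1 shows that this control has the largest training volume of the four arms.

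The Statistical analysis section names two analyses. The first is between groups: "a gain score analysis (change score analysis) using the mean difference between M1 and M2 for between-group differences of the outcomes will be performed", by one-way ANOVA. The second is given as an example, "two-way ANOVA with dependent samples". That model has a time (M1-M2) term as well as group and interaction terms, and the section does not say which term carries which conclusion.

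The Discussion then states two things the trial will deliver. One is "the definition of a minimum dosage required to improve trunk function". The other, added to it, is that "the efficacy or non-efficacy of the sensorimotor exercises targeting neuromuscular factors like strength and neuromuscular activity will be evaluated in detail".

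The only comparison with no intervention is the unpublished pilot in the Background, whose programme was "four exercises; nine sessions over 3 weeks; three sets of 10 repetitions per exercise". The only retest figure, under Trunk strength, is "bias ± 1.96 SD: 8.16 ± 64.8 Nm", from 10 people and for peak torque with perturbation.

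**The concern.** Both Discussion statements are absolute. Whether an exercise programme is efficacious, or which dose is enough to improve function, is a question about training against no training. This trial randomises between four kinds of training. If all arms gain equally, the between-arm analysis cannot tell four equally effective programmes from four ineffective ones with a common retest gain.

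The only quantity left to answer the absolute question is uncontrolled change from M1 to M2. That change contains any training effect, but also learning of an unfamiliar test, familiarity with the perturbation and motivation under maximal-effort testing. Familiarisation is 60 s per condition on the test day, and the article describes no separate familiarisation day or repeated baseline.

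The stakes are highest for the smallest programme. A minimum-dose statement matters most there, and outside evidence is thinnest.

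**Working it through.** **1. What each comparison identifies.** Write the mean gain in arm k as training effect k plus a shift s common to all arms. A difference between arms is effect j minus effect k, so s cancels. A within-arm gain, or the time effect averaged over arms, keeps s. The gain-score ANOVA therefore speaks to relative effects only, and the time term does not separate training from s.

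**2. Does the pilot supply the missing contrast?** Prescribed sets are sessions × exercises × sets (Background; Table 1):

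| Programme | Calculation | Sets |
|---|---|---|
| Pilot | 9 × 4 × 3 | 108 |
| Control | 6 × 4 × 3 | 72 |
| G I | 6 × 3 × 2 | 36 |
| G II | 6 × 2 × 2 | 24 |
| G III | 6 × 1 × 3 | 18 |

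Control has 72/108, or two thirds, of the pilot volume. The six-session threshold comes from a compliance analysis, which is not a randomised dose comparison. The article does not describe G I to G III as pilot arms, and it gives them perturbation in every exercise. It states no margin or bridging rule that would carry the pilot effect over.

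**3. What the retest figures show.** Inputs from Trunk strength: bias 8.16 Nm, 1.96 SD = 64.8 Nm, n = 10.

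- SD of the difference = 64.8/1.96 = 33.06 Nm.
- Standard error of the bias = 33.06/√10 = 10.45 Nm.
- 95% CI with 9 df: 8.16 ± 2.262 × 10.45 = -15.5 to 31.8 Nm.

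The interval includes zero and also includes shifts of practical size.

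**4. Hypothetical illustration.** The article gives 20 per group without a power analysis, so there is no stated effect size or power to reproduce. Assume no training effect, a common second-test gain s, an SD of change of 33.06 Nm and two-sided α = 0.05. The noncentrality is s/(33.06/√n). For s = 8.16 it is 8.16/(33.06/√80) = 2.21 for all 80 participants (76 df), and 8.16/(33.06/√20) = 1.10 for one arm. The noncentral t gives the chance of a significant change:

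| Assumed shift s | Time effect, N = 80 | One arm, n = 20 | One arm at α/4 |
|---|---|---|---|
| 4 Nm | 19% | 8% | 2% |
| 8.16 Nm | 59% | 18% | 7% |
| 16 Nm | 99% | 54% | 31% |

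In 20,000 simulated four-arm trials with s = 8.16 Nm, the time effect was significant in 58.5% and the between-arm gain ANOVA in 5.0%, its nominal level.

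**The case against.** The strongest reply is that the stated purpose is comparative. The Abstract and Background set out to compare programmes against an active control, the Discussion gives dose-response as the main purpose, and the named gain-score ANOVA is unaffected by a common shift. All of that stands. An active control is a legitimate choice for this question, and a clear advantage of one programme over another would be sound randomised evidence of a relative effect.

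A reader might infer that the plan will report a significant time effect as proof of efficacy down to the smallest dose. The documents do not support that. No sentence says so, the two-way ANOVA is only an example, and the choice of decisive term may lie in an analysis plan that is not shown. The valid criticism is narrower: the Discussion promises conclusions for which the design has no comparator, and an analysis plan cannot create one.

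A reader might also take 59% as the expected false-positive rate. It is not. The bias comes from 10 people, concerns perturbation torque only, and has no stated direction or retest interval; a loss on retest would hide training gains instead. The figure ignores the planned Bonferroni adjustment, whose family is not stated. It is also a pooled figure and says nothing about the smallest dose. Significance in each of four arms separately would occur in only about 0.182⁴ = 0.1% of trials if the arms were independent.

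The 60-s familiarisation, identical procedures on both days and a blinded measurement team reduce some of the risk, but they do not measure or remove a retest shift. The pilot, with 750 participants, lends outside support to the four-exercise programme, and both session counts are openly stated. What is missing is a bridge from nine sessions to these arms.

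**Conclusion.** The point holds for the two absolute statements in the Discussion and no further. With training in every arm, the trial can show that one programme gains more or less than another. It cannot by itself show that a programme is efficacious or that a given dose is the minimum needed.

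This follows from the design and does not depend on the 8.16 Nm figure. The retest data add only that a material shift is neither established nor excluded (95% CI about -15.5 to 31.8 Nm). The 59%, 18% and 7% rates are conditional on reading the bias as a second-test gain of 8.16 Nm, on an SD of change of 33.06 Nm and on zero training effect. They illustrate the risk and do not predict it. The randomised dose comparison and its gain-score ANOVA are not invalidated.

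**What to change.** Make three changes of wording:

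1. In Statistical analysis, state that within-arm M1-M2 changes and the time effect of any two-way ANOVA are descriptive and will not support an efficacy or minimum-dose claim.
2. In the Discussion, limit conclusions to randomised differences between programmes. Replace the efficacy and minimum-dosage statements with ones about relative change in trunk function between programmes.
3. Where the pilot is cited, note that its comparison with no intervention used nine sessions, that control here has six, and that it therefore does not by itself establish efficacy for these four arms.

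No new arm, visit or analysis is needed. The cost is a more modest claim.
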